#### Statistical analysis

The primary and secondary endpoints analyses will be conducted by an independent statistician on an intention-to treat basis and using the full data set comprising all randomized participants. In addition, a *per protocol* analysis of the primary outcome will be reported. The data set for this analysis will comprise participants who adhered to all aspects of the protocol and received at least 80% of the training sessions. Multiple imputation of missing values will be conducted. All variables will be expressed as means, SD or median (IQR), unless otherwise indicated. Baseline comparisons between the two arms of the study will be made using means or medians and proportions with 95% confidence intervals as appropriate.

All endpoints and analyses have been prospectively categorized as either primary or secondary. Differences in both primary and secondary endpoints between the two arms of the study will be tested independently at the 0.05 level of significance, using a one-way ANCOVA model that will include the baseline value of the given outcome in question as a covariate. No formal adjustments will be undertaken to constrain the overall type I error associated with the secondary analyses. Their purpose is to supplement evidence from the confirmatory primary analysis to help more fully characterize the treatment effect. Results from the secondary analyses will be interpreted in this context.

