## Background

Rehabilitation after spinal cord injury (SCI) has been traditionally based on expectations regarding functional outcomes predicted by the initial level of injury and severity of impairment [1]. It has relied substantially on compensatory strategies for identified impairments and deficits that were considered irremediable, because significant recovery of motor function was not expected beyond that defined by clinical assessments [2]. Thus, in patients with clinically complete injuries, therapy has been primarily directed at activities to improve functional independence, e.g., teaching new strategies to move in bed and transfer into and out of a wheelchair, and provision of assistive devices [2]. This strategy is reliant on strengthening muscles above the spinal lesion level and using leverage, momentum and substitution to move weak or paralyzed parts of the body. While this approach results in improvements of independent function, it does not promote recovery of motor control in the paralyzed limbs [3]. In addition, because of funding limitations available for in-patient rehabilitation, therapists have had to focus on targeting immediate needs for independence in preparation for discharge [2].

Regular physical activity through upper body training is effective in improving cardiorespiratory fitness, muscle strength [4,5] and psychological well-being in the SCI population [6]. However, there is new evidence that regular and intensive *activity-based therapies*, directed at activation of the paralyzed extremities, promotes neurological improvement [2,7-9]. These therapies include partial body-weight-supported locomotor training (LT), functional electrical stimulation (FES)-assisted leg exercise, and exercises to improve control of trunk and lower limb musculature. To date, the interventions have been investigated as single entities; however, Harness et al. [9] conducted a study involving a combination of these interventions. They reported that people with spinal cord injury receiving intensive exercises focused on attempting to regain voluntary motor function below the level of injury showed improvement in motor function, whereas those undertaking a self-directed exercise program did not show any improvements. However, the study had a number of limitations, including a non-randomized design and significant difference between groups in time post-injury.

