### Design

A multicenter, assessor-blinded, randomized controlled trial will be conducted. Experimental group participants will undertake an intensive 12-week program of whole body exercise, including their paralyzed lower limbs, while control group participants will undertake an upper body strength and aerobic fitness training program over the same period. The trial will be conducted in six spinal units in Australia and New Zealand. Ethical approval has been obtained from the Human Research Ethics Committee at each site (see Additional files 1 and 2) and at the University of Melbourne (HREC 1034730). Participants will be provided with information sheets, and written informed consent will be obtained prior to recruitment and baseline assessment.

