### Randomization

Participants will be randomly assigned to either the experimental or control group with a 1:1 allocation as per a computer-generated randomization schedule stratified by site and injury status [American Spinal Injuries Association Impairment Scale (AIS) A/B or AIS C/D]. The randomization schedule will be under the control of a central randomization unit, independent of the trial, located at Neuroscience Trials Australia. A participant will be considered to have entered the trial once his/her randomization is revealed.

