### Statistical analyses

#### Sample size

This power analysis is for a one-way fixed effects analysis of covariance with two levels that correspond to experimental and control arms of the study. This analysis includes baseline value of AIS Motor Score as a covariate and uses week 12 values as the primary outcome. Available pilot data [9] demonstrate a mean change in the AIS Motor Score of 4.8 (SD = 1.0) in an intensive exercise group compared to a mean change of 0.1 (SD = 0.5) points in the control group from the comparable baseline of 40. Assuming the more conservative difference in mean changes in AIS Motor Score between the groups of 4.0, a similar baseline mean AIS Motor score of 40 and a correlation between the baseline and week 12 ASIA Motor score of 0.8, the resulting analysis of covariance effect size (f) is 0.22. The corresponding total sample size of 150 participants equally distributed between experimental and control arms will yield power of 0.8 to reject the null hypothesis at a 0.05 level of significance. The analysis of variance is non-directional (i.e., two-tailed), which means that an effect in either direction will be interpreted. Allowing for 20% dropout rate, the final sample size for this study is calculated to be 188 patients equally distributed between experimental and control arms.

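### The primary ANCOVA leaves out the stratification factors (site and AIS group), which costs power and makes the test conservative to the extent that the strata are balanced and prognostic

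*Protocol article*

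**What the plan says.** The Randomization section of the Protocol article describes a "computer-generated randomization schedule stratified by site and injury status", where injury status means AIS A/B or AIS C/D. Participants are "randomly assigned to either the experimental or control group with a 1:1 allocation". No block size or other balancing scheme is given. The Design section counts six spinal units, which gives 6 × 2 = 12 strata.

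The Statistical analysis section then says that primary and secondary endpoints are to be tested "using a one-way ANCOVA model that will include the baseline value of the given outcome in question as a covariate". The Sample size section has the same structure: "This power analysis is for a one-way fixed effects analysis of covariance with two levels", with the baseline motor score as covariate. Nowhere does the article add site or AIS group to the analysis.

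**The concern.** Stratified allocation makes the arms alike on the stratification factors. If those factors affect the outcome, this balance reduces the true sampling variability of the treatment difference. A model without the factors cannot show that reduction: their variance stays in the residual, and the standard error is computed as if balance had been left to chance. Confidence intervals are then too wide, the test rejects less often than 5% under the null hypothesis, and some power that the design has already paid for is not used.

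The baseline score may not carry all the information in AIS group. Eligible injuries range from C6 to T12, and the motor score adds 50 upper-limb and 50 lower-limb points, so the same total can arise from different combinations of level and completeness. Site could matter too, because exercises are selected by local clinical judgment. These are reasons to expect some added prognostic value, but they do not show how much.

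**Working it through.** **Inputs from the Sample size section.** Difference 4.0 points; baseline to week 12 correlation 0.8; f = 0.22; 150 analysed in two equal arms; two-sided 0.05.

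**Assumptions (not in the document).** Permuted blocks of 4 within 12 strata; AIS groups and sites of equal expected size; share *s* of the post-baseline residual variance explained by AIS group and site together, varied from 0% to 30%.

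**The plan's own figure.** With two equal arms f = difference / (2 × SD), so the residual SD after baseline is 4.0 / (2 × 0.22) = 9.09, and the raw SD is 9.09 / √(1 − 0.8²) = 15.15. The noncentral F with 1 and 147 degrees of freedom and noncentrality 150 × 0.22² = 7.26 gives power 0.763, not 0.80. That shortfall is a separate matter; 0.763 serves here only as the starting point.

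**Standard errors.** The planned model reports about 2 × 9.09 / √150 = 1.48 whatever *s* is. With the strata exactly balanced, the true standard error is 1.48 × √(1 − s), that is 1.41 at 10% and 1.33 at 20%.

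**Analytic power with the strata in the model.** The effect size becomes f / √(1 − s): 0.226, 0.232 and 0.239 at s = 5%, 10% and 15%. Power rises from 0.763 to 0.784, 0.805 and 0.827.

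**Simulation**, 6000 trials per scenario (simulation error about 0.003 for type I error and 0.005 for power), blocks of 4:

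| Share s | Type I error, planned | Type I error, with strata | Power, planned | Power, with strata |
|---|---|---|---|---|
| 0% | 0.054 | 0.056 | 0.755 | 0.756 |
| 5% | 0.046 | 0.051 | 0.767 | 0.781 |
| 10% | 0.035 | 0.047 | 0.766 | 0.796 |
| 20% | 0.034 | 0.056 | 0.787 | 0.848 |
| 30% | 0.021 | 0.052 | 0.794 | 0.888 |

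Under the null hypothesis the planned model's mean standard error was 1.487, 1.486 and 1.489 at 10%, 20% and 30%, against a true sampling SD of 1.403, 1.362 and 1.276. A second simulation gave type I errors of about 4.2% and 3.4% at 10% and 20%, and power of 77% versus 80% and 78% versus 84%. The direction and the power loss agree; the type I error at 10% is best read as roughly 3.5% to 4%.

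**Baseline related to AIS group.** With a correlation of 0.6 and s = 20%, the planned model had type I error 0.032, and power was 0.776 versus 0.838, so the result is similar.

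**Without balance.** Under simple randomization the planned test kept its level (0.045 to 0.052). Power for planned versus stratum-adjusted models was 0.754 versus 0.737 at 0%, 0.757 versus 0.778 at 10% and 0.752 versus 0.823 at 20%.

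**What the shares mean in points.** With a 50/50 AIS split, a difference of D points between AIS groups at the same baseline score explains (D/2)² / 9.09² of the residual variance: 4/82.6 = 5% for D = 4, 9/82.6 = 11% for D = 6 and 16/82.6 = 19% for D = 8.

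**The case against.** The strongest reply is that neither condition is established. No block scheme is given, and without balance the planned test holds its level. Nothing in the article shows that AIS group or site predicts the week 12 score once baseline is in the model, and at a 0% share nothing is lost. The larger shares also need large effects: an AIS difference of 4 points at the same baseline already equals the whole planned treatment effect, yet by itself it gives only about a 5% share and costs about 1 point of power. All of this stands. It is why the size is a range that starts at zero.

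It may also be said that the model is valid, already contains the covariate around which the sample size is planned, and matches the power calculation. That stands too, but it does not remove the efficiency loss.

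That the matter may be left to an analysis plan does not stand. A one-way model with a single covariate is a positive choice, stated in two sections, and it omits factors that the same document uses to allocate treatment.

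A reader might also infer that time since injury belongs in the model, because the Background lists among the pilot study's limitations "including a non-randomized design and significant difference between groups in time post-injury". The document does not support that step: the remark concerns a non-randomized comparison, and time since injury is not a stratification factor here.

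**Conclusion.** The mismatch between allocation and analysis is certain; its consequence is conditional. To the extent that allocation is balanced within strata and the strata are prognostic beyond baseline, the planned standard error is too wide and the test conservative. At 150 analysed with blocks of 4, the power loss is about 0 points at 0%, 1 at 5%, 3 at 10% and 6 at 20%, where the type I error is about 3.5%. These figures rest on an assumed block scheme, equal-sized strata and an unknown share.

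Two stronger readings are not supported. One is that the primary test is invalid or biased: the estimate is unbiased, and no scenario showed a type I error above 5% by more than simulation error. The other is that the standard error is certainly too wide: that needs both conditions, and the article settles neither. The shortfall from 80% power noted in the working arises from the sample size arithmetic, is not caused by this omission, and should be judged separately. This is a worthwhile efficiency improvement, not a flaw in validity.

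**What to change.** In the Statistical analysis section, replace the one-way ANCOVA with an ANCOVA containing treatment, the baseline value of the outcome, AIS stratum as randomized (A/B versus C/D) and site. Put the same terms in the multiple imputation model, so that imputation and analysis agree.

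The cost is one sentence and about 6 degrees of freedom: 1 for AIS group and 5 for six sites, leaving 141 instead of 147 at 150 analysed. If the strata turn out not to be prognostic, the power cost under blocked allocation is negligible (0.756 with them, 0.755 without). Only if allocation were in effect unblocked would it reach about 2 points (0.737 versus 0.754).

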#### Data integrity and management

Data will be stored electronically on a database with secured and restricted access. Data transfer will be encrypted and any information capable of identifying individuals removed.

#### Withdrawals

A participant will be considered to have withdrawn from the trial when consent is revoked or if the participant cannot be contacted or located. If this occurs, no further assessments will be performed. Participants will not be withdrawn from the trial for protocol violations.

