### Outcome assessments

Assessments will occur at baseline, 12 weeks after the commencement of the intervention, and then at 6 months and 12 months after randomization. All assessments will be undertaken by therapists blinded to group allocation. Any inadvertent unblinding of assessors will be reported. In addition, the success of blinding will be estimated by asking assessors to guess the participant’s group allocation at the completion of each post-randomization assessment.

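### The withdrawal rule treats loss of contact like revoked consent and gives no route back, so obtainable 6- and 12-month outcomes could be forgone

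*Protocol article*

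**What the plan says.** The Withdrawals section defines withdrawal by two triggers: "A participant will be considered to have withdrawn from the trial when consent is revoked or if the participant cannot be contacted or located". The second trigger runs straight into the single consequence given for both: "if the participant cannot be contacted or located. If this occurs, no further assessments will be performed". The only exemption follows directly: "Participants will not be withdrawn from the trial for protocol violations".

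Three other parts of the article bear on this:

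- **Outcome assessments** sets the schedule: "Assessments will occur at baseline, 12 weeks after the commencement of the intervention, and then at 6 months and 12 months after randomization". There are therefore two planned visits after the primary time point.
- **Statistical analysis** says the endpoints will be analysed "on an intention-to treat basis and using the full data set comprising all randomized participants", with multiple imputation for missing values.
- **Sample size** inflates the target with the words "Allowing for 20% dropout rate", and does not say how that loss divides between reasons.

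**The concern.** Revoked consent and loss of contact call for different handling. After consent is revoked, the trial should stop assessing. A person who is out of contact has revoked nothing. If they become reachable while a scheduled visit remains, their outcome can still be measured. The rule as written gives both the same consequence, and nothing elsewhere in the article reopens follow-up for the second group. Protocol violators are expressly kept in the trial, so a consenting person who is temporarily out of reach is treated more strictly than someone who broke the protocol.

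At stake are outcomes at 6 and 12 months, where nearly all secondary endpoints are measured, including the motor score itself. Imputation fills such gaps under assumptions, but it does not replace a value that could have been observed. An analysis plan cannot recover an assessment that the protocol told the site not to make. For that reason this is a point about a stated rule and not about missing detail.

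**Working it through.** **Reading the text.** The sentence giving the consequence refers back to the whole preceding sentence, so it covers both triggers. The exemption that follows covers protocol violations only. Neither the assessment schedule nor the analysis section provides for resuming assessments after contact is restored. The literal reading is therefore that loss of contact ends follow-up for good.

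**The plan's own figure.** Evaluable participants 150, dropout 20% (Sample size): 150 / (1 − 0.20) = 187.5, rounded up to 188. This reproduces the stated total. The expected loss is 188 × 0.20 = 37.6, about 38 people.

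**How many might be regained.** The article does not support a count, so what follows is illustration. It also assumes that the 20% applies at the later visits, for which the article gives no separate rate.

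- Assume one quarter to one half of the 38 are contact losses: 9.5 to 19. Assume half of those are reachable at a later visit: 4.75 to 9.5, or about 5 to 10 people.
- With wider assumptions (25% to 75% contact losses, 25% to 50% of them reached later): 37.6 × 0.25 × 0.25 = 2.4, and 37.6 × 0.75 × 0.50 = 14.1, or about 2 to 14 people.

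**Effect on precision at the visit where they are regained.** With equal arms and an unchanged residual SD, the standard error is proportional to 1/√N. Starting from 150 observed:

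| Regained | Observed N | Ratio of standard errors | Reduction |
|---|---|---|---|
| 2 | 152 | √(150/152) = 0.993 | 0.7% |
| 5 | 155 | √(150/155) = 0.984 | 1.6% |
| 10 | 160 | √(150/160) = 0.968 | 3.2% |
| 14 | 164 | √(150/164) = 0.956 | 4.4% |

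These are observed-data figures. They ignore whatever the imputation already recovers.

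**Which outcome this touches.** The primary outcome is the motor score at 12 weeks. Someone reached again at 6 or 12 months supplies no observed week-12 value, so the table applies to the secondary outcomes at the later visit. The primary analysis can benefit only if the imputation model for a missed week-12 score uses later scores, and the article does not say whether it will.

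**The case against.** The strongest reply is that the trigger, in its ordinary sense, means definitive loss to follow-up. On that reading the consequence mostly states the inevitable. How many attempts over what period count as non-contact is operational detail that an article normally leaves to the full protocol or site manual. This limits the size of the problem, and few people are affected if sites apply the rule only after final loss of contact. It does not remove the point, because the article sets no such threshold and states the consequence without exception.

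Other features also reduce exposure. Withdrawn participants stay in the intention-to-treat analysis through imputation. People unable to attend the long-term follow-up visits are excluded at entry. The 36 supervised sessions over 12 weeks keep those who attend in frequent contact up to the primary time point.

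A reader might be tempted by four stronger readings that the documents do not support:

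- **That one missed appointment, a move or a hospital readmission triggers withdrawal.** The text requires inability to reach or find the person. People in those situations can often still be reached.
- **That a late week-12 assessment is specifically barred.** The Withdrawals section does not address visit windows or late assessments.
- **That the primary analysis loses about 3% in precision.** Contact regained at 6 or 12 months does not produce an observed week-12 score.
- **That the resulting missing data will differ by arm and bias the comparison.** Participants and therapists are unblinded, so this is possible. But the article gives no loss rates by arm, and the control is itself an active, intensive programme.

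The indirect benefit through imputation may also be modest. Exercise is unrestricted after week 12, so a later motor score may partly reflect other training.

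**Conclusion.** The point stands in limited form. The withdrawal rule joins two events that need different handling and, read literally, forgoes 6- and 12-month outcomes from people who still consent and could be assessed. That sits poorly with an analysis "using the full data set comprising all randomized participants".

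The number affected cannot be derived from the article. If 5 to 10 people were regained, the standard error at that visit would fall by about 1.6% to 3%. Under the wider assumptions the range is 0.7% to 4.4%. The true effect could be close to nil if the rule is used only after final loss of contact. Any gain for the primary outcome is indirect and depends on the imputation model. This is a cheap improvement of minor severity. Confidence is moderate, because the text is clear but its working definition is not shown.

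**What to change.** Split the rule in the Withdrawals section:

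1. Revoked consent: the participant is withdrawn and assessments stop.
2. Non-contact: record the visit as missed, keep the participant in the trial, attempt contact at each remaining scheduled visit, and assess if reached. Class the participant as lost to follow-up only once the 12-month visit has passed without contact.

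The sentence on protocol violations can stay as it is. The cost is a small rewording and a few extra contact attempts at visits already scheduled. Treatment, endpoints and sample size are unchanged.

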#### Monitoring

The trial will be overseen and monitored by a Program Manager. The Program Manager will visit each site to examine trial procedures, ensure data quality and monitor compliance with the trial protocol. All adverse events and serious adverse events will be recorded according to standard procedures. Three safety variables will be monitored and documented throughout the trial. These are self-reported pain (using an 11-point category rating scale), blood pressure and skin irritation from the stimulating electrodes or body weight support harness. However, only two safety variables (pain and blood pressure) are considered serious enough to warrant inclusion in two unblinded safety interim analyses. These analyses will be undertaken when 60 and then 120 participants have completed the post-intervention assessment. It will be done by an Independent Data Safety Monitoring Board comprising a statistician and two rehabilitation doctors. If there are concerns about the safety of participants, this board will make a recommendation to the trial steering committee about continuing, stopping or modifying the trial. The Haybittle-Peto procedure for generating early stopping boundaries will be used for pain and blood pressure. A recommendation of early termination for safety reasons because of pain (mean margin of 4/10) or blood pressure (mean margin of 40 mmHg) will be considered by the Independent Data Safety Monitoring Board if the corresponding Haybittle-Peto boundary (*p* = 0.003, Z = 3) at a given interim analysis is crossed. No formal interim analyses for efficacy or futility are planned.

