#### Experimental group

Participants in the experimental group will receive a triad of interventions comprising locomotor training, FES-assisted cycling as well as trunk and upper and lower extremity exercises. These interventions will be provided at the participating spinal units.

*Locomotor training* will be provided using a Therastride system (Innoventor, Inc., St Louis, MO, USA). Participants will be assisted to stand on the treadmill in an upright position and suspended in a harness by an overhead pulley at the maximum load necessary to avoid the knees collapsing into flexion. A therapist/assistant will be positioned behind the participant to stabilize the pelvis and trunk, as well as to assist weight shifting and hip rotation during the step cycle. This person will ensure that the trunk and pelvis are not flexed or hyperextended during stepping. Two therapists/assistants will be seated in front and to the side of the participant to provide manual assistance for the lower limbs to facilitate knee extension during stance and knee flexion and toe clearance during swing, maintaining appropriate alignment of the limbs. Manual assistance will be used as needed. Another therapist/assistant will control the treadmill. During the session, the treadmill speed will be adjusted to promote the best stepping pattern at the given body weight load. Speed will be progressively increased as appropriate to a normal walking speed range (0.89-1.34 m•s^-1^). Over the course of the study, the amount of body weight support can be reduced gradually as the participants improve their ability to bear weight on the lower limbs [21].

*FES-assisted cycling* will be provided using a RT300 cycle (Restorative Therapies, Baltimore, MD, USA). Surface electrodes will be applied over the belly of the quadriceps, gluteal and hamstrings muscles according to a standardized protocol. The pedal cadence will be set to 15–50 rev•min^-1^. Stimulation intensity will be gradually increased to a maximum of 140 mA with a pulse width of 0.3 ms at a frequency of 35 Hz [22,23]. Participants will exercise at the maximal power output possible at their level of recovery. They will undertake 30 min of cycling, initially in intermittent periods of exercise with rest breaks, but progressing to longer continuous exercise as deemed appropriate by supervising therapist/assistant. The frequency, power output, interval times and total training duration will be recorded at each training session.

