#### Control participants

Participants in the control group will receive an upper body strength and fitness program provided three times per week for 12 weeks. This program may be provided at the spinal unit or an appropriately equipped gymnasium as approved by the Project Committee. The program will be a circuit-based exercise program incorporating resistance and cardiorespiratory training. For this protocol, the circuit will comprise several stations using different pieces of equipment and with minimal time to rotate between stations. The participants will be supervised by a therapist and/or clinical exercise instructor, and exercises will be progressed as appropriate to build strength and endurance in the intensity range of 6–20 repetition maximum (RM). Exercises could include hand cycling, chest press, boxing, lateral pull-downs and rowing. Guidelines for the content and delivery of exercises will be clearly outlined in a handbook to ensure standardization across sites.

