#### Leg exercise capacity test at 12 weeks, 6 months and 12 months

Participants will perform a graded exercise test using their legs (FES cycling), following the protocol of Heesterbeek et al. [25]. The electrical stimulation current amplitude will be increased manually from the lowest current amplitude that evokes minimum muscle contraction up to 100% amplitude of the cycle’s stimulator output (~140 mA). The timing of FES stimulation current amplitude increments will be based on the prevailing heart rate response between resting heart and age-predicted maximum heart rate. The measures of interest will be change of peak power output (W), peak heart rate (b•min^-1^) and change of sub-maximal heart rate (b•min^-1^) during the 20 W and 40 W stages and during the incremental portion of the leg cycling.

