## Discussion

This trial will provide information about the effectiveness of an intensive full-body exercise program in promoting neurological improvement. This is important for understanding the therapeutic effect of rehabilitation independent of drug or cellular interventions, since rehabilitation may confound the outcome of these interventions [45]. The mechanisms by which exercise programs improve function after SCI also need to be better understood because they allow for development of new and more effective therapeutic strategies. In this study, the control intervention is not standard care but an active intervention, involving an intensive exercise program for the upper body. This ensures that the intensity and group dynamics of the both exercise programs are similar, so that the effects of adding exercise of the paralyzed lower limbs can be identified.

This trial will adhere to key methodological principles important for minimizing bias (International Conference on Harmonisation Good Clinical Practice annotated by the Therapeutic Goods Administration of Australia) [46] and will be reported according to the CONSORT guidelines [47]. For example, allocation will be concealed and randomized, assessors will be blinded, and analyses will be performed on an intention-to-treat basis. Therapists and participants will not be blinded because of the nature of the intervention. One primary outcome and a number of secondary outcomes will be used. The primary outcome reflects neurological function. The secondary outcomes include measures of impairment, activity limitation and participation restriction, and encompass both objective measures as well as participants’ perceptions. Importantly, all adverse events will be rigorously documented so that the safety of the interventions can be evaluated. It is anticipated that this trial will take 3 years to complete.

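### The monitored skin variable counts only irritation from electrodes or harness, so other skin harm, and nearly all skin harm in controls, rests on general adverse event recording and is open to detection bias

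*Protocol article*

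**What the plan says.** The Monitoring section sets up two levels of safety recording. The first is general: "All adverse events and serious adverse events will be recorded according to standard procedures". The second is specific: "Three safety variables will be monitored and documented throughout the trial". The three are self-reported pain, blood pressure and "skin irritation from the stimulating electrodes or body weight support harness".

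Skin is then left out of the interim looks, because "only two safety variables (pain and blood pressure) are considered serious enough to warrant inclusion in two unblinded safety interim analyses".

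The two devices named in the skin variable come from the Experimental group section. Locomotor training has the participant "suspended in a harness by an overhead pulley at the maximum load necessary to avoid the knees collapsing into flexion", and the cycling component uses surface electrodes over the leg and gluteal muscles. The Control participants section mentions neither device: "Participants in the control group will receive an upper body strength and fitness program provided three times per week for 12 weeks", with hand cycling, presses, pull-downs and rowing as examples. Outside the programs, the leg exercise capacity test uses FES cycling and is not restricted to one arm.

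The Discussion gives the purpose of safety recording: "all adverse events will be rigorously documented so that the safety of the interventions can be evaluated". It also states that neither those who deliver the programs nor those who receive them are blinded.

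**The concern.** Pain and blood pressure are defined without reference to cause, so they mean the same thing in both arms. The skin variable is defined by its cause, and both causes lie almost wholly in one arm. A mild skin event from seating, a transfer or gym equipment does not meet the definition in either arm. A control participant can meet it only through the leg exercise test.

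The three named variables are monitored in addition to general adverse event recording, so the plan intends closer attention for them. For skin, that closer attention follows the experimental devices. Mild skin changes are easily missed unless someone asks or looks, and the people who would ask or look know the allocation. A later statement that one program causes more or less skin harm than the other would then mix the true difference with a difference in how hard it was looked for.

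Skin matters to this population in both arms. The exclusion criteria bar only existing pressure ulcers of stage 3 or 4, so people with lower-stage ulcers may enter.

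**Working it through.** The plan gives no figure for skin events, so there is nothing to reproduce. The check is to trace each kind of skin event through the text.

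**Step 1. Which events meet the monitored definition?**

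| Skin event | Arm | Monitored skin variable | General adverse event record |
|---|---|---|---|
| From electrodes or harness in training | Experimental | Yes | Yes |
| From electrodes at the leg exercise test | Either | Yes | Yes |
| From seating, transfers or other equipment | Experimental | No | Yes |
| From seating, transfers or gym equipment | Control | No | Yes |

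No row is lost altogether. What differs is the level of ascertainment: apart from the leg test, only the experimental arm has rows with specific monitoring.

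**Step 2. What does this do to a between-arm comparison?** Let:

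- *d* be the true risk of device-related skin events in the experimental arm;
- *o*E and *o*C be the true risks of other skin events in the two arms;
- *s* be the chance that an event is recorded when it is specifically monitored;
- *u* be the chance that it is recorded through general adverse event reporting alone.

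Leaving aside the few control exposures at the leg test:

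- recorded risk, experimental = *s·d* + *u·o*E
- recorded risk, control = *u·o*C
- recorded ratio = *o*E/*o*C + (*s/u*)·(*d/o*C)
- true ratio = *o*E/*o*C + *d/o*C

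The two ratios agree when *s* = *u*. If specific monitoring finds more than general reporting (*s* > *u*), the device term is multiplied by *s/u* and the recorded ratio exceeds the true one. With one common level of ascertainment in both arms and for all causes, *s/u* becomes 1 and the distortion goes.

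**Step 3. Can it be sized?** No. The document gives none of *d*, *o*E, *o*C, *s* or *u*. The direction rests on the assumption *s* > *u*. That is plausible for mild skin changes, but the text does not state it.

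**Step 4. Does a decision in the trial depend on it?** Not at the interim looks, where the Haybittle-Peto boundaries apply to pain and blood pressure only. The effect is confined to the final description of harms.

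**The case against.** The strongest reply is that all adverse events are recorded without limit by arm, cause or body system. The Discussion's promise to evaluate safety rests on those records, not on the three monitored variables. This stands. A reader might infer that skin harm cannot be compared between arms at all; the document does not support that.

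A second reply is that watching for a foreseeable local effect of two devices is a legitimate purpose in itself, and that no between-arm test of the skin variable is stated. This also stands. A reader might infer that the plan contains a skin comparison loaded against the experimental arm by construction, but no such analysis is written. A reader might also count device sessions in each arm and present the imbalance as the size of the bias. That fails for three reasons. More device irritation where devices are used is a real effect of the program. The text does not say that harness and electrodes are both used at every session. And the baseline leg test should not count, because the document sets baseline apart from the post-randomization assessments.

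A third reply is that the monitoring is to run throughout the trial with no stated restriction to one arm, and that the method of checking skin and eliciting adverse events belongs to the full protocol and case report forms, which are not shown. This stands as regards method, and nothing here is held against the article for leaving such detail out. It does not answer the point about definition. The article states what the variable counts, and following that wording in both arms still gives controls almost nothing to record under it.

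**Conclusion.** The point holds as unequal ascertainment set by a stated definition. The specifically monitored skin variable is tied to devices of the experimental program. Skin injury from other causes, and nearly all skin injury in controls, depends on general adverse event recording. A comparison of skin harm between arms remains possible but is open to detection bias, because therapists and participants know the allocation.

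The conclusion assumes that the variable is recorded as worded and that specific monitoring detects more mild skin events than general reporting. The size is unknown. The primary outcome is untouched and no interim stopping decision depends on skin. This is a cheap improvement of low severity.

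**What to change.** In the Monitoring section, and on the matching case report form:

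- Define the third safety variable as any new skin irritation or pressure injury, from any cause.
- Ask about it on the same schedule in both arms.
- Record the suspected cause (electrode, harness, seating, equipment, other) in a separate field, so that attribution no longer decides whether an event is counted.
- Compare the arms on the any-cause variable and report device-related events as a subset, which keeps the device information the present wording was meant to give.

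The cost is one form field and a brief question at control sessions; the downside is slightly more recording in the control arm. The change concerns recording only.

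It has to be made during data collection, because mild events that were never asked about in controls cannot be recovered at analysis. The Trial status section has recruitment starting in January 2011 and running to the end of 2013. For any participants whose program ended before the change, the comparison would still rest on adverse event records, and the date of the change should be reported.
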